## Characteristics of an Adverse Event

### Relationship to Study Intervention

To assess the relationship of an event to the study intervention, the following guidelines are used:

- Related (Possible, Probable, Definite)
  - The event is known to occur with the study intervention.
  - There is a temporal relationship between the intervention and event onset.
  - The event abates when the intervention is discontinued.
  - The event reappears upon a re-challenge with the intervention.
- Not Related (Unlikely, Not Related)
  - There is no temporal relationship between intervention and event.
  - An alternate etiology has been established.

### Expectedness of SAEs

The study PI will be responsible for determining whether an SAE is expected or unexpected. An adverse event will be considered unexpected if the nature, severity, or frequency of the event is not consistent with the risk information previously described for the intervention.

### Severity of Event

The following scale will be used to grade adverse events:

- **Mild**: no intervention required; no impact on activities of daily living (ADL)
- **Moderate**: minimal, local, or non-invasive intervention indicated; moderate impact on ADL
- **Severe**: significant symptoms requiring invasive intervention; subject seeks medical attention, needs major assistance with ADL

## Reporting Procedures

### Unanticipated Problem Reporting to IRB

Incidents or events that meet the criteria for unanticipated problems require the creation and completion of an unanticipated problem report form. The following information will be included when reporting an adverse event, or any other incident, experience, or outcome as an unanticipated problem to the IRB:

- appropriate identifying information for the research protocol, such as the title, investigator’s name, and the IRB project number;
- a detailed description of the adverse event, incident, experience, or outcome;
- an explanation of the basis for determining that the adverse event, incident, experience, or outcome represents an unanticipated problem;
- a description of any changes to the protocol or other corrective actions that have been taken or are proposed in response to the unanticipated problem.

To satisfy the requirement for prompt reporting, unanticipated problems will be reported using the following timeline:

- Unanticipated problems that are serious adverse events will be reported to the IRB within 1 week of the investigator becoming aware of the event.
- Any other unanticipated problem will be reported to the IRB within 2 weeks of the investigator becoming aware of the problem.
- All unanticipated problems should be reported to appropriate institutional officials (as required by an institution’s written reporting procedures) within 1 month of the IRB’s receipt of the report of the problem from the investigator.

### Reporting of Pregnancy

The EPA has stated that, “Based on our review of scientific studies, there is no evidence of reproductive or developmental effects to mother or child following exposure to permethrin [36].” In addition, the CDC recommends the use of permethrin-treated clothing by pregnant women in regions at risk for mosquito-borne diseases [26]. Therefore, there will not be any monitoring for, reporting of, or modifications to study eligibility relating to pregnancy status.

## Halting Rules

The occurrence of any severe adverse event or at least five study-related moderate adverse events will prompt a temporary suspension of enrollment pending review by the Data Safety & Monitoring Board. The objective of the safety review is to decide whether the study should continue per protocol, proceed with caution, be further investigated, be discontinued, or be modified and then proceed. Suspension of enrollment is a potential outcome of a safety review.

# STUDY OVERSIGHT

In addition to the PI’s responsibility for oversight, study oversight will be under the direction of the Data Safety and Monitoring Board (DSMB) at the North Carolina Translational & Clinical Sciences Institute (TraCS), led by [name]. The DSMB is independent of the study and will be available in real time to review and recommend appropriate action regarding adverse events and other safety issues will review enrollment reports every 6 months and full data reports annually. Any moderate or severe adverse events related to study participation should be reported promptly and an ad hoc review be conducted, if deemed necessary. Reviewed data will be separated by study arm and provided by a statistician with access to the unblinded data.

# STATISTICAL CONSIDERATIONS

## Study Hypotheses

We hypothesize that the intervention will reduce malaria incidence among infants and young children relative to children receiving untreated *lesus*.

## Sample Size Considerations

The sample size was selected to provide sufficient power to evaluate the primary study hypothesis. We plan to recruit and enroll 400 mother-infant pairs. Additional participants will be enrolled in the study to replace those who drop out before 12 weeks. Those who drop out after 12 weeks will not be replaced. All participants who attend any clinic visits post randomization will be included in the primary, intention-to-treat (ITT) analysis.

Assuming a baseline risk of approximately 3.0 cases per 100 person-weeks as estimated from our pilot study, the trial will have power of at least 0.80 to detect a 30% relative reduction in the incidence rate of malaria between intervention and control groups over the proposed study period of 24 weeks with a type I error rate of 0.05 and assuming a two-sided test based on the asymptotic test statistic of the intervention parameter from a Poisson regression model with an offset for time at risk [49]. Power for other effect sizes is presented in the table below. This assumes an average of 23.1 weeks of follow-up per participant per arm, based on the observed drop-out in the pilot study. Calculations were conducted using nQuery software and are based on previously described methods [50].

No interim analyses are proposed, so no adjustments were made to these calculations to account for interim testing. This effect size was assessed as the minimum at which the intervention would be persuasive to take to scale, especially as it represents an incremental effect above and beyond LLIN use.

Anticipated Power to Detect Differences in Malaria Incidence Rate between Intervention and Control Arms

| **Rate Ratio** | **Anticipated Power** |
| --- | --- |
| 0.80 | 0.42 |
| 0.75 | 0.62 |
| 0.70 | 0.80 |
| 0.65 | 0.92 |

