# STUDY DESIGN

The proposed study is a double-blind, randomized controlled trial of permethrin-treated *lesus* to prevent *P. falciparum* malaria in children 6–18 months of age at study enrollment conducted at two sites in rural western Uganda. Participants will be randomized to one of two arms: permethrin-treated (intervention) or untreated (control) *lesus.* Participating mother-infant pairs will receive a new LLIN and two permethrin-treated or untreated *lesus* at enrollment. The total sample size will be 400 mother-infant pairs with 200 pairs in each arm. We will follow participants longitudinally for six months. Participants will be instructed and incentivized to present to one of the two study clinics when a fever develops, where they will be evaluated, tested, and treated, if positive, for malaria. Participants will also attend scheduled clinic visits every two weeks for routine surveillance of adverse effects and to test for asymptomatic infection. Re-treatment and sham re-treatment of *lesus* will occur each month.

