### Analysis of primary outcome (AIM 1)

In the primary analysis, the rates of clinical *P. falciparum* malaria in children 6–24 months of age will be compared between treatment arms by estimating the incidence rate ratio and a corresponding 95% confidence interval (with the control arm as the referent group) of malaria using a Poisson regression model. The outcome, the number of observed incident cases of malaria, is a count variable. Individuals will be censored from the analysis for a period of 28 days after an incident malaria episode to account for the reduced risk of infection following treatment with AL. The Poisson model will include adjustments to control for stratification variables from randomization (study site and age group) and will include an offset to account for varying person-time-at-risk across subjects. The robust variance estimator will be used to account for potential overdispersion.

In exploratory analyses, we will further evaluate our primary outcome by fitting additional Poisson regression models to estimate associations between the incidence of malaria and measured covariates, including the frequency of *lesu* use and washing and residual permethrin concentration among participants in the intervention arm.

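### The power of at least 0.80 at a rate ratio of 0.70 is not what the analysis in section 10.3.1 delivers: about 0.74, or 0.77 to 0.78, depending on how the pilot rate was defined

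*Protocol*

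**What the plan says.** Protocol section 3 fixes the size: "The total sample size will be 400 mother-infant pairs with 200 pairs in each arm". Section 10.2 gives the other inputs. The control rate is introduced as "Assuming a baseline risk of approximately 3.0 cases per 100 person-weeks as estimated from our pilot study". The test is described "with a type I error rate of 0.05 and assuming a two-sided test based on the asymptotic test statistic of the intervention parameter" in a Poisson model with an offset for time at risk. On follow-up it says: "This assumes an average of 23.1 weeks of follow-up per participant per arm, based on the observed drop-out in the pilot study". The stated result is that "the trial will have power of at least 0.80 to detect a 30% relative reduction in the incidence rate of malaria", and the table lists power of 0.42, 0.62, 0.80 and 0.92 at rate ratios of 0.80, 0.75, 0.70 and 0.65. The same section calls the 30% reduction the smallest effect that would justify scale-up.

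Section 10.3.1 then fixes the primary analysis. On time at risk: "Individuals will be censored from the analysis for a period of 28 days after an incident malaria episode". On variance: "The robust variance estimator will be used to account for potential overdispersion".

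**The concern.** Section 10.2 explains the step from 24 to 23.1 weeks by drop-out alone. It does not mention the 28 days removed after every episode, although its own model carries an offset for time at risk. Nor does it allow for counts more variable than Poisson. Both features belong to the analysis that the protocol itself prescribes, so the claimed power and the planned test do not describe the same thing.

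What is at stake is how a null result is read. At the effect that the sponsor regards as the minimum worth acting on, the stated chance of missing it is 20%. If the real chance is higher, a non-significant result would be taken as stronger evidence against the intervention than it is.

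**Working it through.** **Inputs.** 200 per arm (section 3); control rate 0.03 per week, 23.1 weeks, two-sided 0.05, rate ratio 0.70 (section 10.2); 4 weeks not at risk after each episode, robust variance (section 10.3.1). Dispersion: none given, so any value is an assumption.

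**1. The plan's own figure.** Expected control events a = 200 × 23.1 × 0.03 = 138.6; intervention events b = 0.70 × 138.6 = 97.0; |ln 0.70| = 0.3567. Take an asymptotic test of the log rate ratio with null variance 4/(a+b) and alternative variance 2/a:

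power = Φ[(0.3567 − 1.96 × √(4/235.6)) / √(2/138.6)] = Φ[(0.3567 − 0.2554) / 0.1201] = Φ(0.843) = 0.8005.

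| Rate ratio | Stated | This formula | Wald |
|---|---|---|---|
| 0.80 | 0.42 | 0.4175 | 0.417 |
| 0.75 | 0.62 | 0.618 | 0.602 |
| 0.70 | 0.80 | 0.8005 | 0.769 |
| 0.65 | 0.92 | 0.923 | 0.889 |

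All four rows match to two decimals. The formula is optimistic because its alternative variance 2/a gives the intervention arm the control arm's event count.

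**2. Same inputs, the planned test.** The Wald variance uses each arm's own events: SE = √(1/138.6 + 1/97.0) = 0.1324, and power = Φ(0.3567/0.1324 − 1.96) = 0.769. Simulating the Poisson test with robust variance (20,000 trials, constant rates, site and age group not modelled) gives 0.777.

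**3. The 28-day exclusion, with 3.0 read as a rate per week at risk.** Each child was simulated with 4 weeks not at risk after each episode. Mean time at risk falls to about 20.8 weeks (control) and 21.5 weeks (intervention). Events are then about 200 × 20.8 × 0.03 ≈ 125 and 200 × 21.5 × 0.021 ≈ 90.
- Wald: SE = √(1/125 + 1/90) = 0.138; power about 0.73.
- Simulation with robust variance: about 0.74.
- The formula of step 1: Φ[(0.3567 − 1.96 × √(4/215)) / √(2/125)] = Φ(0.706) = 0.76.
- Neighbouring rows: about 0.56 at rate ratio 0.75 and 0.86 at 0.65.
- With a full 24 weeks for every child: about 0.75 at rate ratio 0.70.

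**4. The 28-day exclusion, with 3.0 read as a rate per calendar week.** The rate per week at risk must then be higher, about 0.0335, so that expected control events stay near 138.6 after the exclusion. Simulated power is about 0.78, essentially the value of step 2.

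**5. Overdispersion (assumed values, at-risk reading, exclusion applied).** With between-child gamma variance of 0.25, 0.5 and 1.0, simulated power at rate ratio 0.70 is about 0.68, 0.62 and 0.53.

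**6. Detectable effect.** Without overdispersion, 80% power is reached at a rate ratio of about 0.68 on the at-risk reading and about 0.69 on the calendar reading.

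**The case against.** The strongest reply is that the table is not miscalculated. A reader who applies the usual Wald formula gets 0.77 and might infer an arithmetic error. The documents do not support that: step 1 reproduces every row from the stated inputs. The protocol cites software and published methods that are not at hand, so the choice of approximation cannot be called a slip. This stands in full. What remains is that the match at 0.70 is 0.8005, with nothing in hand for any loss left out.

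It can also be said that the fall to 0.74 is conditional. Section 10.2 does not say whether the pilot's person-weeks were calendar time or time at risk, and on the calendar reading the exclusion costs almost nothing. This also stands, and is why both readings are shown. It does not rescue the claim, because the planned test reaches only about 0.77 to 0.78 on that reading.

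A reader might further infer that the plan expects overdispersion and that power is therefore between 0.53 and 0.68. The protocol calls it only potential and gives no size; a robust variance is a safeguard, not a forecast. Those figures illustrate sensitivity and are not estimates for this trial.

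Finally, section 10.2 replaces children who drop out before 12 weeks, which adds person-time. Even a full 24 weeks for everyone gives only about 0.75 with the exclusion on the at-risk reading.

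**Conclusion.** The point holds as a mismatch between the power statement and the planned analysis. At a rate ratio of 0.70, the test in section 10.3.1 has power of about 0.73 to 0.74 if the pilot rate is per week at risk, and about 0.77 to 0.78 if it is per calendar week. Power of at least 0.80 is not delivered on either reading. The chance of missing a true 30% reduction is thus roughly 26% or 22 to 23%, against the implied 20%, before any overdispersion.

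These figures take the 3.0 rate as correct, hold rates constant over follow-up and ignore the stratification terms. The shortfall is moderate. It does not affect the type I error, the estimate or the choice of model, but it does change a figure on which the trial relies.

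**What to change.** In Protocol section 10.2:

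- State whether the pilot's 3.0 per 100 person-weeks is per week at risk or per calendar week.
- Recompute power for the analysis in section 10.3.1, with time at risk net of the 28-day exclusion and the robust variance test.
- Replace the claim of at least 0.80 and the table with the result: at rate ratio 0.70, about 0.74 on the at-risk reading or about 0.77 to 0.78 on the calendar reading.
- Add a sensitivity range for overdispersion, labelled as assumed.
- State the rate ratio detectable with 80% power.

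The cost is a rerun of the calculation, new wording and a less favourable stated power. No additional participants are needed.

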## Final Analysis Plan

Analyses will be conducted using an ITT approach, with woman-infant pairs analyzed according to the arm they were randomly assigned to (i.e., treated or untreated *lesu*) regardless of their subsequent use or non-use of the *lesus* and dropout. *Lesu* use will be evaluated as a secondary outcome, and if *lesu* use is lower than anticipated, exploratory analyses may use marginal structural models to estimate an “as-treated” effect of permethrin-treated *lesus* on the primary endpoint.

An α=0.05 significance level will be used throughout, with corresponding 95% confidence intervals. No adjustment for multiple testing will be made for the primary outcome. For secondary outcomes (excluding safety endpoints), we will control the false discovery rate using methods from Benjamini and Hochberg (1995).

Given the level of subject participation in the pilot study, we expect most mother-infant pairs to complete all study activities. Missing data due to dropout or missed clinic visits are anticipated to be uncommon (≤5% missing), so a complete case analysis is planned. If >10% of participants are missing data in either arm, a sensitivity analysis will be conducted using multiple imputation assuming data are missing at random (missing conditional upon measured baseline covariates and study outcomes). If data are suspected to be missing not at random, this will be described with the study results as a limitation.

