### Participant Incentives

Participants will be eligible to receive the following incentives for participation:

| Event | Eligibility | Amount (UGX* / USD) |
| --- | --- | --- |
| Baseline Home Visit | Visit Completed | 10,000 / $3.00 |
| Bi-Weekly Study Visit (12) | Attends Visit (Transport Supplement) | 8,000 / $2.25 |
| Bi-Weekly Study Visit (12) | Communication Supplement | 2,000 / $0.60 Airtime |
| Bi-Weekly Study Visit (12) | Completed *Lesu* Use/Wash Diary | In-Kind (e.g., Soap, Sugar) |
| Final Visit / Exit Interview | Attended ≥80% of visits | 20,000 / $6.00 |
| **POTENTIAL TOTAL** | | 180,000 / $50.00 |

**Approximate UGX to USD conversion; may change based on exchange rate*

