### Handling of Subject Withdrawals or Subject Discontinuation of Study Intervention

Given the established safety profile of the intervention there is minimal risk of continued *lesu* use outside the parameters of the study. Therefore, subjects who withdraw or otherwise discontinue participation will not be followed further.

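### Section 10.3 plans a complete case analysis for dropout and missed visits, which read literally conflicts with the protocol's own ITT set and person-time offset

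*Protocol*

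**What the plan says.** Four statements in the protocol bear on who and what enters the primary analysis.

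- Section 10.2 sets the analysis population: "All participants who attend any clinic visits post randomization will be included in the primary, intention-to-treat (ITT) analysis". The same section replaces participants who drop out before 12 weeks, but not later ones.
- Section 10.3, first paragraph, analyses pairs in the arm to which they were randomised, whether or not they used the lesus and whether or not they dropped out.
- Section 10.3.1 specifies a Poisson model for the number of malaria episodes, with "an offset to account for varying person-time-at-risk across subjects".
- Section 10.3, third paragraph, then states: "Missing data due to dropout or missed clinic visits are anticipated to be uncommon (≤5% missing), so a complete case analysis is planned". Multiple imputation is a sensitivity analysis, used if more than 10% of participants in either arm have missing data.

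Section 10.3.2 applies the primary-outcome methods to asymptomatic parasitaemia in children and clinical malaria in mothers, and says that complete data are expected there as in the primary analysis. For the haemoglobin and growth changes it excludes participants with missing data at a timepoint when such data are few.

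On follow-up, Section 4.5.2 says that "subjects who withdraw or otherwise discontinue participation will not be followed further". Section 4.5 follows participants to closeout, withdrawal of consent or death, and allows data collected before withdrawal of consent to be kept and used.

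**The concern.** Dropout and missed visits are the situations that the first three statements are built to handle. A child who leaves at week 10 has ten weeks at risk and some number of observed episodes, and the offset lets that child contribute exactly this. A complete case rule for the same situations points the other way. The protocol does not define a complete case for a count with an offset, so an analyst could follow either rule and cite the protocol for it.

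If the exclusion reading were followed, three things would go wrong.

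- The comparison would be restricted to children selected on attendance after randomisation. This can bias the rate ratio if leaving or missing visits differs by arm or is related to malaria risk.
- Observed events and time would be lost.
- Where a dropout before week 12 has been replaced, the randomised child would be left out and the replacement counted.

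A missed scheduled visit also does not make the primary outcome missing. Section 2.2 counts episodes found at unscheduled study-clinic visits and documented episodes from other clinics.

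**Working it through.** **1. Inputs, all from the protocol.** 200 pairs per arm and 24 weeks of follow-up, with a mean of 23.1 weeks after dropout. Control rate: "Assuming a baseline risk of approximately 3.0 cases per 100 person-weeks as estimated from our pilot study". Target: "the trial will have power of at least 0.80 to detect a 30% relative reduction in the incidence rate of malaria", "with a type I error rate of 0.05 and assuming a two-sided test".

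**2. The plan's own power.** With person-time T per arm, expected events are e0 = 0.03 × T (control) and e1 = 0.70 × e0 (intervention). For the log rate ratio with pooled null variance:

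power = Φ( [ |ln 0.70| − 1.96 × √(4/(e0 + e1)) ] / √(1/e0 + 1/e1) )

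T = 200 × 23.1 = 4,620 person-weeks gives e0 = 138.6 and e1 = 97.0. Power = Φ((0.3567 − 0.2554)/0.1324) = 0.778.

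Other standard two-sided tests give 0.769 to 0.778, against 0.80 stated. With the full 24 weeks the same formula gives 0.793. The stated figure is therefore not reproduced exactly at 23.1 weeks. The gap is small and nothing below rests on it, because the comparison is between two rules under one formula.

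**3. Observed person-time kept, versus dropouts removed.** Assumptions: a fraction d of each arm drops out, on average at week 12, equally by arm and unrelated to risk. No replacements are added and no time is deducted for the 28 days after an episode. The 5% is the plan's upper expectation for missing data, 10% is its imputation trigger, and 7.5% is the value that gives a mean of 23.1 weeks (0.925 × 24 + 0.075 × 12 = 23.1).

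- Kept: T = 200(1 − d) × 24 + 200d × 12
- Removed: T = 200(1 − d) × 24

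| Dropout | T kept | T removed rule | Power kept | Power, dropouts removed |
|---|---|---|---|---|
| 5% | 4,680 | 4,560 | 0.783 | 0.773 |
| 7.5% | 4,620 | 4,440 | 0.778 | 0.762 |
| 10% | 4,560 | 4,320 | 0.773 | 0.751 |

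**4. Observed data lost per arm under removal.** At 5%: 10 × 12 = 120 person-weeks (120/4,680 = 2.6%), or 3.6 control and 2.5 intervention events. At 10%: 20 × 12 = 240 person-weeks (240/4,560 = 5.3%), or 7.2 and 5.0 events.

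**5. Bias.** This cannot be sized. The documents give no dropout by arm and nothing on how dropout relates to malaria risk. The pilot reports only that 48 of 50 pairs completed and that the other two did baseline activities alone.

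**The case against.** The best defence is that complete case here only means observed data without imputation. Section 10.3 sets it against multiple imputation. Section 10.2 states the inclusion rule outright, and an offset for varying time would be nearly pointless if only completers entered. Where the protocol means exclusion, in Section 10.3.2 for the change outcomes, it says so. This stands far enough that exclusion is not certain. It does not remove the conflict. Section 10.3 names dropout and missed visits as the cause of missingness and counts it by participant. Section 10.3.2 shows that the protocol handles missing data by exclusion elsewhere, and ties its complete-data wording to the primary analysis.

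A reader might infer a large loss of power, on the view that one missed visit makes a child incomplete. No section says that. If the expected 5% counts participants, such a rule would require a miss rate of only about 0.4% per visit over the 12 follow-up visits (1 − 0.95^(1/12)), which suggests that the authors did not have it in mind. The incentive condition "Attended ≥80% of visits" does not help that reading, since it is a payment threshold and not an expected attendance rate or a missing-data rule.

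A reader might also infer that Section 4.5.2 throws away observed data, or drives unequal loss through skin reactions to permethrin. It does not discard data: it leaves later time unobserved, and Section 4.5 allows earlier data to be used. Its operative sentence concerns people who leave the study, not those who merely stop using the lesu. Section 4.5.1 does allow an investigator to end participation for an adverse event, but Section 4.5 expects withdrawals to be uncommon, and the pilot had one mild rash, not confirmed on examination. Unequal loss by that route is possible, unquantified and probably small.

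**Conclusion.** The point holds as a conflict between stated rules. The complete case sentence in Section 10.3, taken at its word, removes children whom Sections 10.2 and 10.3 include and whose partial time Section 10.3.1 is designed to use. It would also count a replacement in place of the randomised child. The main reason to correct it is selection on attendance after randomisation, whose size the documents do not allow anyone to state.

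The power cost of removing dropouts alone is minor: about 1 percentage point at 5% and 2 at 10%, on the assumptions listed. It would be large only under a one-missed-visit rule that the protocol does not contain.

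The ambiguity in Section 4.5.2 is a separate and lesser matter. Its heading covers discontinuing the intervention, while its text ends follow-up for those who discontinue participation. Section 10.3 counts on pairs who stop using the lesu remaining in the analysis.

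**What to change.** For the primary outcome, and for asymptomatic parasitaemia in children and clinical malaria in mothers, replace the complete case sentence. The new sentence should say that every participant in the Section 10.2 ITT set, including those later replaced, contributes all observed events and time at risk up to last contact through the offset. The Section 10.2 set itself need not change. How time around a missed visit is counted can be left to the SAP.

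Confine complete case to the week 12 and week 24 change outcomes, and keep multiple imputation as a sensitivity analysis for the primary outcome.

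Separately, reconcile the heading and text of Section 4.5.2 with Sections 4.5 and 10.3, so that it is clear that stopping use of the lesu without withdrawing from the study does not end outcome follow-up. This concerns data collection only and leaves any clinical rule on stopping the lesu as it is.

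The cost is a few sentences. The analysis change needs no new data and no change to the sample size. The Section 4.5.2 clarification adds at most a little follow-up for the few who stop using the lesu.
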